#### Secondary Outcomes

Secondary outcome variables included in this study will be other pain related outcomes, different body composition measurements, energy balance-related behavior, medical consumption, indirect health costs, and quality of life. Table 2 shows the timeline of the collection of all outcomes and Table 3 displays the entire list of all outcomes and a detailed description of their assessment.

**Table 3 TB3:** Overview and Description of Primary and Secondary Outcome Measures*^a^*

**Construct**		**Measure**	**Description**
**Primary Outcome**			
Pain intensity		Brief Pain Inventory-short form (BPI)	Assessed with 1 question of the BPI: “Please rate your pain by crossing the number that best describes your pain of the last 24 hours on the AVERAGE (0-10).”^42^ The BPI is assessed using the REDCap software.
**Secondary Outcomes**			
Pain-related outcomes			
	Pain interference	Brief Pain Inventory-short form (BPI)	Pain interference is used to assess how much pain interferes with 7 daily activities. It is typically scored as a mean of the 7 items on a 11-point scale (range 0–10), when at least 4 questions have been answered.^42^ The BPI is assessed using the REDCap software.
	Pain extent	Pain drawings on a digital tablet	The Navigate Pain software is used to create pain drawings on a digital tablet (Navigate Pain, Aglance Solutions AALBORG, Denmark). This software enables detailed drawings of pain intensity and the area of discomfort on a 3-D body chart. Analyses can be performed for anatomical and neuroanatomical subdivisions, visualizing pain, and quality of pain with heat maps and can detect map locations, distribution, and patterns of pain and discomfort. This method is feasible and generates reliable and valid data.^46–48^
	Kinesiophobia	Tampa Scale for Kinesiophobia (TSK)	The TSK contains questions about pain-related fear of movement, fear of (re-)injury, and fear avoidance behavior and is frequently used in samples of patients with LBP.^49–51^ A 2-factor model is recommended for patients with CLBP, resulting in 2 subscales: somatic focus (belief of underlying medical problem) and activity avoidance (belief that activity may result in pain or [re]injury).^52^^,^^53^ The TSK is assessed using the REDCap software.
	Fear avoidance beliefs	Fear Avoidance Belief Questionnaire (FABQ)	The FABQ focuses on the beliefs of patients with LBP about how physical activity and work affect LBP (fear of pain caused by physical activity).^54^ Psychometric properties of the German version with a 3-factor model was found to be fair to good, with an internal consistency of 0.91 for the total scale and a good test–re-test reliability of all items (*r* = .87).^54^ The FABQ is assessed using the REDCap software.
Body composition			
	Height	Body height	Height is measured in cm using a stadiometer (SECA 206/213, Hamburg, Germany).
	Weight Body Mass Index (BMI) Body fat and fat free mass	Bioimpedance analysis (BIA)	Bio-impedance analysis is a convenient, low-cost, non-invasive, and reliable tool to assess body composition.^55^ The TANITA Bio-electrical Impedance Analyzer (TANITA MC-780SMA, TANITA Europe B.V., Amsterdam, Netherlands) is used to measure body weight, body fat percentage, and fat free mass (%). Body height and weight will be used to calculate BMI (kg m^−2^). More details can be found in Suppl. Material 7.
	Body fat distribution	Cescorf measuring tape (waist and hip circumference)	Cescorf measuring tape (CESCORF, Porto Alegre/RS, Brazil) is used to assess waist- and hip circumference and to calculate the waist-to-hip ratio, to account for body fat distribution. The body fat distribution should be considered for analyzing the obesity-CLBP relationship.^56^ More details can be found in Suppl. Material 7.
	Adipose tissue thickness Muscle thickness	Uncompressed subcutaneous adipose tissue thickness using a portable ultrasound scanner Muscle thickness of *Musculus multifidus* using a portable ultrasound scanner	To account for regional body composition measurements, uncompressed subcutaneous adipose tissue thickness of triceps, biceps, subscapular, supraspinal, abdominal, and medial calf is assessed using a portable ultrasound scanner (MicrUs Ultrasound scanner TELEMED Ltd, Vilnius, Lithuania), which generates highly reliable and valid data.^57–59^ More details can be found in Suppl. Material 7. In addition, muscle thickness of the *M. multifidus* is assessed using the same ultrasound device.^60–62^ More details can be found in Suppl. Material 7.
Energy balance related behavior			
	Dietary intake	Prospective food diary for 3 day	Dietary intake will be assessed with a 3-day prospective food diary (see Suppl. Material 8). Dietary intake is monitored on 2 representative weekdays and 1 weekend day which can be selected by the participants. The dietary intake includes all food and all drinks/fluids that participants consume. They are advised to weigh their meals and snacks whenever possible and otherwise to describe their portion sizes as detailed as possible (eg, 1 tablespoon of honey). The food diary is sent via WeTransfer service (WeTransfer B.V. Amsterdam, Netherlands) to the study personnel.
	Rest activity cycles	Fitbit Sense (wrist-worn activity monitor)	To capture continuous rest/activity cycles an accelerometry (Fitbit Sense 1 or 2, Fitbit International Limited, Dublin 2, Ireland) is used. This wrist-worn package will be installed 1 week prior to the treatment, will continue throughout the 14 weeks treatment, and will end the day of the follow-up body composition measurement (T1). Participants are instructed to wear the device constantly (day and night) and to synchronize the watch with the app once a day to ensure data storage. At T5, the last follow-up measurement, the Fitbit is handed out again and the participants are instructed to wear the accelerometer for 1 additional week.
	Sleep quality	Pittsburgh Sleep Quality Index (PSQI), Fitbit	The PSQI is a widely used tool to assess sleep quality.^63^^,^^64^ The PSQI is assessed using the REDCap software.
	Sleep quantity	Fitbit Sense	Sleep quantity and quality will be monitored using the Fitbit watch, including sleep schedules, time spent in bed, sleep duration, wake duration, and number of awakenings. While these devices are not recommended for diagnosing sleep disorders, they are suitable for monitoring sleep–wake behavior over extended periods.
	Continuous physical activity	Fitbit Sense	Continuous physical activity and rest/activity cycles are measured with an activity monitor (Fitbit Sense 1 or 2). Data analysis occurs through Fitabase software. Next to physical activity, sedentary behavior will be investigated with the accelerometer data.
Costs			
	Medical consumption	Medical Consumption Questionnaire (MCQ)	Medical consumption (including co-interventions) will be recorded using the Medical Consumption Questionnaire, which is a generic instrument for measuring patients’ total (in-)direct medical consumption.^38^ The MCQ is assessed using the REDCap software.
	Indirect health costs	Productivity Cost Questionnaire (PCQ)	The Productivity Cost Questionnaire will be used to obtain data regarding the indirect costs (eg, costs due to absenteeism or presenteeism).^65^ Costs will be reported in non-aggregated form and will be calculated as “units consumed × unit cost.” Unit costs will be extracted from country specific databases for health care services and drugs. All costs will be expressed in 2026 Belgium euro and for Swiss data also in 2026 Swiss Francs. Intangible costs (eg, pain, stigma) will be omitted. The PCQ is assessed using the REDCap software.
Quality of life			
	Quality of life	EuroQol EQ-5D-5L questionnaire	The EuroQol EQ-5D-5L questionnaire is used to assess quality of life and health profiles, which will be transformed to utilities using Belgium, UK, and German tariffs.^66^^,^^67^ Health utilities are then used to calculate quality adjusted life years for the cost-utility analysis. The EQ-5D-5L is assessed using the REDCap software.
**Additional Outcomes**			
Blinding—group allocation guess		Self-developed questionnaire: Do you think you received the therapy of the experimental or control group?	To measure the level of blinding at the end of the trial, participants answer 1 question for group allocation. They are asked in which group they think they were and how certain they are about this judgement on a scale from 0% to 100% (0% means they are very unsure vs 100%, which means a 100% certainty). This question is assessed using the REDCap software.

^a^
For Swiss participants, questionnaires in German will be used and for Belgian participants, questionnaires in Dutch will be used, respectively. Abbreviations: CLBP = chronic low back pain; LBP = low back pain; UK = United Kingdom.

### Statistical Analysis

#### Sample Size Calculation

A priori sample size calculation for the primary outcome (ie, pain intensity) was performed in GPower version 3.1.9.2 showed that a total sample size of 252 participants (126 in each country) is needed to achieve 95% power to detect a small effect size (partial *η*^2^ = 0.02), using a linear mixed model with alpha level .05 considering a 25% drop-out rate across 12 months of follow-up. Although the effect sizes for the primary outcome measure pain intensity in the proof-of-concept studies were medium to large^13^^,^^25–27^^,^^29^ we anticipate a smaller effect size in the present research proposal (partial *η*^2^ around 0.02), considering the fact that the control intervention has already been shown to be effective in reducing pain.^13^ Taking into account the drop-out rates in the proof of concept studies (9% to 23%),^13^^,^^26^^,^^27^ and the fact that the current proposal combines a weight reduction program with education plus exercise therapy, we anticipate a relatively higher drop-out rate of 25%. Allocation ratio (N2/N1) was defined as 1, resulting in 63 patients in each treatment group per country. A previous trial investigating the effectiveness of a healthy lifestyle intervention for patients with CLBP reported a sample size calculation of 80 participants, accounting for 15% loss to follow-up.^68^ This sample size provided 90% power to detect a clinical meaningful difference in pain intensity of 1.5 points on the Numeric Pain Rating Scale as primary outcome and 80% power to detect a 6% reduction in body weight as a secondary outcome. Based on the small effect size (partial *η*^2^ = 0.02), statistical analyses of other secondary outcome measures in this study should be adequately powered with a sample size of 252 participants.

#### Statistical Analysis Plan

Prior to the analyses, visual inspection for assessing data plausibility will be performed, while the normality assumption will be checked using Q-Q-plots**.** Missing values will be checked for randomness by performing a logistic regression analysis, modeling the probability of missingness against baseline characteristics. If no significant associations are found, missingness will be assumed to be at random**.** Independent samples *t*-tests (for continuous variables) and chi-square tests (for categorical variables) will be performed at baseline to check whether the randomization was successful. If not, variables for which this was not the case will be included as confounders in the main analyses after the direction of the relationship was established using directed acyclic graphs (DAGs).^69^ Drop-out analysis will be performed using independent samples *t*-tests and chi-square tests on the baseline data, while the amount of and reasons for drop-out (participants are asked to give their reasons of withdrawal) will be compared between the experimental and control condition. This procedure will allow us to check whether differential drop-out (and thus attrition bias) is present. Again, variables subject to selection bias will be included as confounders (when identified as such by the DAGs) in the main analyses. General(ized) linear mixed modelling will be performed in R (RStudio version 1.1.383) to evaluate and compare (long-term) therapy effects between the experimental and control intervention. Both the distribution of the outcome measure and residual distributions will be checked for normality using Q-Q-plots. To account for clustering effects (ie, participants will be measured repeatedly, clustered within different hospitals or therapeutic settings), a multilevel model will be constructed, including three levels: (1) repeated measures, (2) clustered within the individual, and (3) clustered within a hospital or other therapeutic setting. This technique is particularly well fitted to analyze repeated measures over time in a hierarchical structure including missing values.^70^ To minimize issues related to multiple testing, contrast testing within the generalized linear mixed model framework will be applied. A priori defined contrasts between the groups will be tested using the R package “multcomp” and the function “glht.” Statistically significant differences will be defined at alpha level .05, and the effect size as well as clinically significant differences will be determined. In addition, numbers needed to treat will be calculated, after transforming the outcome to a binary variable, in analogy with previous research.^71^ Analyses will be performed based on the intention-to-treat principle. Afterward, per protocol analyses will be performed (as a form of sensitivity analysis) to evaluate the effect of therapy adherence and compliance.

For the health economic evaluation, cost-effectiveness and cost-utility planes will be created to illustrate the incremental values of costs and clinical outcomes including the results of a probabilistic sensitivity analysis. If neither of the 2 treatment groups is dominant, incremental cost-effectiveness ratios and incremental cost-utility ratios will be calculated. The analysis will be conducted separately per country and from both health care and societal perspective with a time horizon of 66 weeks.

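### A non-significant regression on baseline variables cannot show that pain scores are missing at random, but the plan uses it to decide exactly that

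*Protocol article*

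**What the plan says.** The Statistical Analysis Plan section of the protocol article checks missing values with a logistic regression, "modeling the probability of missingness against baseline characteristics". It then gives a decision rule: "If no significant associations are found, missingness will be assumed to be at random".

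A separate step in the same section looks at drop-out: "Drop-out analysis will be performed using independent samples *t*-tests and chi-square tests on the baseline data". The amount of drop-out and the reasons for it are also compared between arms. The article says of this step: "This procedure will allow us to check whether differential drop-out (and thus attrition bias) is present". The consequence for the model is that "variables subject to selection bias will be included as confounders (when identified as such by the DAGs) in the main analyses".

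The main analysis is a three-level mixed model on the intention-to-treat principle, described as follows: "This technique is particularly well fitted to analyze repeated measures over time in a hierarchical structure including missing values". Under Primary Outcomes, pain is collected at T0, T1, T2, T3 and T5, and the primary endpoint is the change to 12 months (T5).

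Under Sample Size Calculation, the authors combine earlier drop-out rates of 9% to 23% with the added burden of the weight programme and write "we anticipate a relatively higher drop-out rate of 25" per cent.

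**The concern.** The rule treats a testable question (is missingness related to baseline variables?) as if it answered an untestable one (given what was observed, is missingness related to the pain scores that were not observed?). It can mislead in two ways. It can withhold the MAR label where drop-out depends on baseline pain, a case that a mixed model containing baseline pain handles well. It can also grant the label where drop-out depends on unseen 12-month pain, the case that the model does not handle.

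This matters here because a quarter of participants are expected to be lost by the primary time point. The article links the higher figure partly to a programme that only the experimental arm receives, so loss that differs by arm is plausible, although the article does not predict it. A report that follows the rule could present MAR as verified when it has only been assumed.

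**Working it through.** **Inputs.** From the article: 252 participants, 1:1 allocation, 25% drop-out over 12 months, alpha 0.05. Assumed here, because the article gives no figures: the size of the baseline difference (0.3 SD), the departures from MAR (1 and 2 points) and the simulation settings below.

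**Step 1: numbers lost.** 0.25 × 252 = 63 drop-outs; 252 − 63 = 189 completers.

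**Step 2: what each mechanism predicts for the planned regression.**

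| Mechanism | Association with baseline? | What the rule concludes |
|---|---|---|
| MCAR | None, apart from chance findings | At random |
| MAR through baseline variables | Yes | Label withheld, although MAR holds |
| MNAR, through the part of T5 pain that baseline does not predict | None, apart from chance findings | At random, although MAR fails |

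The first and third rows look the same to the test, so it cannot separate them. In the second row the rule points the wrong way.

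**Step 3: how weak a non-significant result is.** For one covariate with a true difference of 0.3 SD between drop-outs and completers (two-sided 5%, normal approximation):

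- SE = √(1/63 + 1/189) = 0.1455 SD
- 0.3 / 0.1455 = 2.06
- Power ≈ Φ(2.06 − 1.96) = Φ(0.10) = 0.54

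The difference is missed about 46% of the time. With several covariates, chance findings accumulate: for five independent ones, 1 − 0.95⁵ = 0.23.

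**Step 4: possible shift in the T5 contrast.** If a fraction p of one arm is missing and those patients are δ points worse than MAR predicts, that arm's mean is understated by p × δ. With p = 0.25 in the experimental arm only:

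| δ (points) | Shift (points) |
|---|---|
| 0.5 | 0.125 |
| 1.0 | 0.25 |
| 1.5 | 0.375 |
| 2.0 | 0.50 |

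With the same p and δ in both arms, the shifts cancel.

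**Step 5: simulation of the rule.** Settings, all assumed except N and the number of visits: N = 252, five visits, exchangeable correlation 0.5, SD 2.0, no true effect, about 25% missing at T5, an estimate using all earlier visits, five baseline covariates including pain, 1,500 runs.

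| Drop-out mechanism | Any of five covariates significant | Mean bias (points) |
|---|---|---|
| MCAR | 22% | 0.00 |
| MAR through baseline pain | 99.8% | 0.00 |
| MNAR, experimental arm, unrelated to baseline | 23% | −0.26 (SE 0.27) |
| MNAR, same form in both arms | 70% | 0.01 |

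Under the one-arm MNAR mechanism the rule declares missingness at random in about 77% of runs, nearly the same as under MCAR (78%). Under harmless MAR it almost never does. The sizes depend on the assumed settings; the failure to discriminate follows from Step 2.

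**Step 6: what the drop-out analysis adds.** Comparing amounts and reasons by arm can reveal differential loss. Equal loss does not exclude attrition bias, and unequal loss does not prove it. The route to adjustment has two filters: a variable must be flagged by a test and must be called a confounder by the DAG. Allocation is randomised, so a baseline variable that predicts both drop-out and pain may not be classed as a confounder of treatment at all. Such variables are the ones that make MAR more plausible.

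**The case against.** The strongest reply is that the rule changes little. The article names no other estimator for the case in which associations are found; the mixed model is the primary analysis either way, and its validity under MAR does not depend on the regression. It uses the repeated pain scores, so poor response already recorded at T1 to T3 before a patient leaves is taken into account. Drop-out after a poor response is therefore not automatically MNAR. All of this stands. It limits the point to what the plan claims about its missing data and how covariates are chosen. It does not repair the inference.

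Three stronger readings are tempting, and the documents do not support them:

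- **That drop-out is never examined.** The same section compares the amount of and reasons for drop-out between arms, expressly to look for attrition bias.
- **That the per-protocol analysis is offered as the safeguard against missing data.** The article says "per protocol analyses will be performed (as a form of sensitivity analysis) to evaluate the effect of therapy adherence and compliance", which is a question of adherence.
- **That no MNAR analysis is planned.** Only a journal article is at hand; a full statistical analysis plan may contain one, so its absence here is not a fault in itself.

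Nor can the shifts in Step 4 be stated as a share of the planned effect. The article gives no SD for pain in this trial, and its partial η² of 0.02 is stated for a linear mixed model, not as a difference in points at T5.

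**Conclusion.** The rule is wrong as written and should be fixed. A non-significant regression on baseline data supports MCAR only weakly, says nothing about MNAR, and is not needed for MAR. That conclusion rests on the definitions and needs no assumed numbers.

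The consequence for the 12-month result is conditional. A reader might infer that the result will be biased towards the experimental arm. That would require missingness related to unseen pain, different between the arms, and with the experimental arm's drop-outs doing worse than predicted. The article establishes none of these: its 25% applies to the whole trial. Under that scenario the shift is 0.25 points per point of departure at 25% loss in the experimental arm; under similar MNAR in both arms it is close to zero. The 46% miss rate holds for one covariate with an assumed 0.3 SD difference.

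**What to change.** 1. Delete the significance-based rule. The logistic regression may stay as a description of who drops out.
2. State MAR as an assumption of the primary mixed model, and say explicitly that the model uses all pain measurements, including baseline.
3. Name in advance a short list of baseline predictors of drop-out and include them whatever their p-values, in place of selection by test and DAG.
4. Keep the comparison of amounts and reasons by arm, but describe it as a signal of differential drop-out, not as a test for attrition bias.
5. Examine departures from MAR with a delta-adjusted (tipping-point) or reference-based sensitivity analysis of the T5 contrast. If the full analysis plan already has one, refer to it here.

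The cost is wording in the analysis plan and some programming. No new data are needed, and sample size, endpoint and primary estimator stay as they are.

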### Randomization and Blinding

Patients will be randomly assigned to either the experimental or control group, utilizing a computer-generated number sequence. Randomization is stratified for weight category (overweight/obesity), sex (female/male), country (Belgium/Switzerland), and therapy center. The randomization lists with patient numbers and group allocation will only be accessible by an independent researcher. This researcher coordinates all appointment times with the therapist and assessors in both countries to avoid contact between assessors and therapists, assuring assessors’ blinding. In addition, the participants and the statistician will be blinded for allocation. For participants, this is possible as only a vague description of the therapy is provided in the ICF. Moreover, the therapists providing the experimental treatment are not involved in providing the control intervention and vice versa. The interventions will take place at different times during the day to avoid contamination between groups, and patients will not see each other at the hospital or private practice waiting rooms, nor at the university for measurements. Furthermore, blinding success for both patients and assessors will be evaluated by asking whether they believe the patient received the experimental or control intervention, along with their level of certainty (0% being very unsure, 100% being absolutely sure about the group assignment).

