### Outcome Assessment and Data Collection

#### Primary Outcomes

Pain intensity will be measured using the Brief Pain Inventory (BPI) item: “Please rate your pain by circling the number that best describes your pain of the last 24 hours on average (0-10)” will serve as primary outcome.^42^ The primary endpoint is the between-group change in pain intensity from baseline to 12 months follow-up. The BPI is widely used to assess clinical pain and recommended for effectiveness trials in chronic pain^43^ and its reliability and validity has been established.^44^^,^^45^ A reduction of 30% in average pain intensity is considered clinically relevant.^43^ The BPI will be collected online using REDCap at baseline (T0), directly after the intervention (T1, immediate effects), and at 3-months (T2), 6-months (T3), and 12-months (T5) follow-up to capture short-, mid-, and long-term effects, respectively.

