There are some limitations to this study. A relatively high drop-out rate of 25% is expected due to the combination of education with exercise therapy, plus a weight reduction program. However, this is accounted for the sample size calculation, and efforts will be made to reduce drop-out. Additionally, the BWRP will be delivered by physical therapists without established experience in delivering this intervention. Yet, available training protocols, treatment manuals, and feasibility checks of therapy sessions should ensure highest treatment quality. Although some sociodemographic factors will be collected, data on ethnicity will not be included, which limits the ability to explore ethnic disparities across intervention groups and may impact the ability to fully assess the success of the randomization process. Nonetheless, the randomization procedure is assumed to deliver balanced intervention groups for any (un)measured variable.

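### Baseline significance tests between arms decide which covariates enter the main analyses; the covariates should be named in advance instead

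*Protocol article*

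**What the plan says.** The Statistical Analysis Plan section of the protocol article says that independent-samples t-tests and chi-square tests "will be performed at baseline to check whether the randomization was successful". It continues: "If not, variables for which this was not the case will be included as confounders in the main analyses", with the qualifier "after the direction of the relationship was established using directed acyclic graphs (DAGs".

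A second route follows the drop-out analysis, which also applies t-tests and chi-square tests to baseline data: "variables subject to selection bias will be included as confounders (when identified as such by the DAGs) in the main analyses".

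Under Randomization and Blinding, allocation uses a computer-generated sequence, and "Randomization is stratified for weight category (overweight/obesity), sex (female/male), country (Belgium/Switzerland), and therapy center". The mixed model is described by its levels, "1) repeated measures, (2) clustered within the individual, and (3) clustered within a hospital or other therapeutic setting"; no list of fixed effects is given. Under Primary Outcomes: "The primary endpoint is the between-group change in pain intensity from baseline to 12 months follow-up". The limitations paragraph of the Discussion says that "the randomization procedure is assumed to deliver balanced intervention groups for any (un)measured variable".

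**The concern.** A significance test between randomized arms at baseline tests a null hypothesis already known to be true if the sequence was followed. A small p-value then says nothing about whether randomization succeeded, and it does not identify the variables that predict 12-month pain. A variable unrelated to pain with p = .04 is put forward for the main analysis; a strongly prognostic one with p = .06 is not. The Discussion's own assumption of balance sits badly with a test of whether balance was achieved.

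At stake is the fixity of the primary model. Its covariates, and so the exact estimate and standard error, depend on p-values from the trial's own data. This is a stated rule, not a detail left open: a fuller analysis plan would have to reverse it, not complete it.

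**Working it through.** The article gives no figure of its own on this point. Its sample size enters below only as the size of the simulated trials.

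**1. Chance of at least one flag.** Table 2 lists 10 participant characteristics. The article does not say which variables are tested; .05 is its general significance level. For k independent tests under valid randomization, P(at least one p < .05) = 1 − 0.95^k.

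- k = 5: 1 − 0.95^5 = 0.226
- k = 10: 1 − 0.95^10 = 0.401
- k = 15: 0.537
- k = 20: 0.642

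Sex is one of the 10 and is also a stratification factor, so it can hardly be flagged. With k = 9 the result is 1 − 0.630 = 0.370. Related items (occupation, employment status, education) lower it further; testing baseline outcomes as well would raise it.

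**2. What the rule does to inference at a single time point.** Inputs from Sample Size Calculation: 252 participants, 25% drop-out, partial η² = 0.02.

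- Completers: 252 × 0.75 = 189
- f = √(0.02/0.98) = 0.143, so d = 2f = 0.286

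Trials of 189 were simulated with stratified blocked randomization. The stratification factors were assumed to explain 5%, 10% or 20% of outcome variance, and a further baseline covariate 25%. Entries are type I error / power, in that order of assumed R².

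| Model | R² 0.05 | R² 0.10 | R² 0.20 |
|---|---|---|---|
| Unadjusted | 0.041 / 0.501 | 0.037 / 0.495 | 0.032 / 0.491 |
| Covariates chosen by baseline p < .05 | 0.036 / 0.500 | 0.033 / 0.495 | 0.022 / 0.493 |
| Stratification factors prespecified | 0.047 / 0.520 | 0.051 / 0.538 | 0.051 / 0.578 |
| Same, plus the prognostic covariate | 0.046 / 0.650 | 0.052 / 0.666 | 0.046 / 0.729 |

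Bias was negligible throughout (at most 0.004). Under the p-value rule the model's standard error overstates the real spread: at R² 0.05 with no treatment effect, 0.1453 on average against an empirical 0.1367. Hence the low type I error. These powers belong to a single-time comparison and do not check the article's 95%, which rests on a repeated-measures calculation.

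**3. Whether the stratification factors matter for the stated contrast.** The primary endpoint is change from T0 to T5 in a mixed model. Trials of 252 with 25% drop-out and visits T0, T1, T2, T3 and T5 were simulated (60 per setting, correlation 0.5, participant random intercept, no center level, factor effects constant over time). Mean standard error of the T0-to-T5 group contrast, without and with the three factors:

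- R² 0.05: 0.13886 and 0.13877, a change of 0.06%
- R² 0.10: 0.13852 and 0.13831, a change of 0.15%
- R² 0.20: 0.13912 and 0.13859, a change of 0.38%

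The participant effect absorbs factors that do not change over time. By the same reasoning the single-time power gains in step 2 should not be carried over to this contrast.

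**The case against.** Four arguments stand against the point.

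- **The DAG step filters what enters.** This is correct, and it is why 40% is not the chance of a changed model. But the DAG is consulted only after a variable is flagged, so the p-value remains the trigger. Randomization also means that no baseline variable causes allocation. A correct DAG therefore shows no baseline confounder: either the step admits nothing, or chance imbalance makes the choice.
- **No harm to validity is shown.** This stands. The simulated rule was unbiased and conservative. The statistician is also blinded to allocation, which limits steering of covariate choice.
- **The drop-out rule is different.** This stands in part. Adding baseline predictors of drop-out can make the missing-at-random assumption more plausible, which matters with 25% expected drop-out. The chance-imbalance argument does not reach that rule. What remains is that these covariates too are triggered by tests rather than named beforehand.
- **Silence on fixed effects is not exclusion.** A reader might infer that weight category, sex and country are left out of the model, because the only covariate routes described are test-triggered. The article does not support that. It gives no fixed-effect list at all, it is a condensed text, and it models the therapeutic setting as the third level. If each center lies in one country, that level probably absorbs part of any country effect.

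**Conclusion.** The point holds in a limited form: the plan lets baseline significance tests nominate covariates for the main analyses, and under valid randomization those nominations are chance. With 10 independent tests at .05, about 40% of trials would flag at least one variable. Independence, the number of variables and the test level are all assumptions.

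The cost is a primary model that is not fixed in advance. In the single-time setting there is also conservatism (type I error 0.022 to 0.036) and lower power (about 0.49 to 0.50, against 0.52 to 0.58 with the stratification factors prespecified). Those figures rest on assumed R² values and on selection by p-value alone, without a DAG filter.

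Two stronger readings should be resisted. Inflated false positives or bias are not shown. A loss of precision worth 2% to 10% of the sample might be inferred from assumed R² values of 0.02 to 0.10 for the stratification factors, but that formula fits a single-time analysis. For the stated T0-to-T5 contrast the simulated standard error changes by less than 0.5%, provided the factors' effects are constant over time.

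**What to change.** - Delete the baseline t-tests and chi-square tests as a gate, and describe baseline characteristics by arm only.
- Before unblinding, fix the covariates of the primary mixed model: weight category, sex and country as fixed effects, therapy center kept as the clustering level, and any prognostic baseline variables named in advance.
- Use baseline pain once, either as the T0 outcome within the repeated measures or as a covariate, and say which.
- Name covariates related to drop-out in advance on DAG grounds, or report test-triggered ones as a sensitivity analysis.

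The cost is a few sentences in the analysis plan. The stratification factors are already recorded for randomization and the Table 2 characteristics are already collected. The article reports 79 of 252 participants included, so the change can be made well before unblinding.
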